Research data will be shared with the steering committee and a statistician for interpretation and analysis. In this study, data will be collected via electronic questionnaires delivered to the participants’ personal or institutional email address. Members of the steering committee, other than the PI, will have no direct contact with expert participants regarding this Delphi study process. Steering committee members will support the PI in the development of the initial questionnaire, help with data analysis and with formalizing future iterations of the questionnaire. All personal identifiers will be removed from the data sets and replaced with placeholder values. The controller of the data is the institution of the PI of the study. Finally, participants will be informed that the PI may reach out to them for further communications following the completion of the study when clarification of responses or feedback is needed for proper analysis of the study data, or for further data analyses related to this study only. Figure 1 presents the Delphi study schema.

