There are no official guidelines available for researchers to use when selecting experts for a Delphi study, or determining appropriate sample size [68]. Based on a systematic review of the Delphi literature, Junger et al. confirmed that, at a minimum, the criteria used for the selection and recruitment of experts should be explained in the methodology, along with survey response rates and information related to the participants expertise [61]. For this study, we will lean on clinical and academic experience/knowledge related to headache and dry needling, along with authorship of peer-reviewed publications, which are commonly used criteria to define expertise in Delphi studies [68]. We aim to recruit and retain 30 experts from multiple countries, which is similar to the number of participants included in previous Delphi studies on the topic of headache [18,40] and DN [65]. Moreover, selecting an expert panel size larger than 30 may not improve the Delphi results and potentially contributes to lower survey response rates [69]. Importantly, a homogenous group of 30 experts with specialized knowledge and experience, in our case DN for headaches (CGH, TTH and migraine), is sufficient to obtain stable results from a Delphi survey [70]. Thirty participants that best represent the expert population most appropriate for this study will be chosen, following agreement to participate.

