### 2.3. Subject Enrollment

A purposive sample of individuals will be invited via email to participate in this Delphi study. An email invitation will be sent to the potential panelists and will include a Delphi study fact sheet to provide information about the study. Following agreement to participate, a participant demographic questionnaire will be issued to assess eligibility for the study. Prior to the round one questionnaire, participants will answer questions related to basic demographics (age, sex, country of residence, current institution, or clinic) along with professional credentials, experience related to clinical practice, relevant academic experience, and DN experience for headache management. Upon confirmation of interest and eligibility, a REDCap survey will be sent electronically to the participant for rounds one through three. The principal investigator will be responsible for executing and managing all aspects of the survey process through REDCap. For participants who are non-English speaking, a translated version of the invitation email, and surveys for the study will be provided. Following consent to participate, each panelist will be asked to commit to participation in each round of the Delphi. Experts will be informed that participation is completely voluntary and there are no consequences for withdrawing from the study at any time or refusing to participate. Participants will be provided with a Delphi study information fact sheet explaining the type of data being collected and the reason for carrying out such a study. Potential participants will be provided with a clear explanation of the anticipated process, and an explanation that participation would last a period of 3–4 months.

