Experts will rate their level of agreement for the included items using a 5-point Likert-scale, except for the initial open questions that will be included as part of the first round. Answers to open questions will be analyzed by the Principal Investigator (PI) and steering committee and converted to closed questions for the next survey round. After each item and open-ended question, there will be space for expert comments. Participant responses from the open-ended questions will be coded alongside each other and analyzed to identify concepts, categories and themes [88]. The PI will organize the data into a Microsoft Excel table and present it to the steering committee. An iterative process will ensue to determine what additional closed question items can be created for round two of the questionnaire based on the thematic analysis. Following the final round of the study, data from REDCap will be exported for statistical analysis.

We define that consensus has been reached when 75% percent of participants “strongly agree” or “agree” with an item. A percentage agreement value of 75% is commonly chosen for determining consensus among Delphi studies, according to a recent review [89]. Participants will not need to vote further on items achieving consensus in round one, and therefore items achieving consensus will not be included in the round two questionnaire. Items achieving 75% agreement or more for “disagree” or “strongly disagree” will be removed. Items that received an overall rating of “unsure” or that were rated as “strongly agree” or agree” by less than or equal to 50% of participants during the first and second round will require further investigation by the steering committee and items/questions will be amended for the next round. That is, if items that are believed to be important fall just below the threshold for consensus, the PI and steering committee will consider including these items as posteriori considerations provided that sufficient justification is provided. A table will be created to provide explanations for amended items moving into the next round. Following each round, the steering committee will review all questionnaire data, participant responses and comments, and the PI will make edits accordingly to prepare for the next survey round.

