#### 2.4.2. Round Two

Themes originating from the open-ended responses and analysis of data from the structured questions of round one will guide the formation of the round two questionnaire. In round two, participants can modify their answers from round one based on results and feedback from that round. Participants will be able to see the amount of consensus on statements from the previous round, and where they answered compared to the group. Participants will not need to vote further on items achieving consensus in this round, and therefore items achieving consensus will not be included in the round three questionnaire. Items achieving 75% agreement or more for “disagree” or “strongly disagree” will be removed. Items that received an overall rating of “unsure” or that were rated as “strongly agree” or “agree” by less than or equal to 50% of participants during the first and second round will require further investigation by steering committee and items/questions will be amended for the next round. A table will be created to provide explanations for amended items moving into round three.

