#### 2.4.3. Round Three

In round three, participants can modify their answers from round two based on results and feedback from that round. Participants will be able to see the amount of consensus on statements from the previous round, and where they answered compared to the group. If consensus is still not reached on a particular item, items will be reviewed and revised according to the criteria by the PI and steering committee and a fourth round will be performed. If all items have reached consensus according to our methods after round three, the questionnaire process will be complete. However, a fourth round may be performed to investigate expert agreement on an official list of recommendations for DN in headache management comprising all consensual items.

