### 2.5. Statistical Analysis

Standard descriptive statistics will be used to describe the demographic characteristics of participants based on the first group of questions of the round one questionnaire. Anonymous answers from the open-ended questions following round one will be analyzed thematically as described in the study procedures section of this protocol. Percentage agreement calculations will be the primary measure throughout all rounds of this Delphi study [90]. However, depending on the data, measures of dispersion and central tendency may be used in place of or in addition to percentage agreement, using Interquartile Range (IQR) and/or Median, respectively, as these measures are also widely used in Delphi studies to define consensus [68]. Data will be analyzed using SPSS 30.0.0 or other statistical software at the end of each round. Wilcoxon rank-sum tests will be used for the final round to evaluate stability and consistency of responses between the final two rounds, with the aim of moving toward consensus [68]. The response rates of participants will also be measured following each round, which is increasingly investigated in Delphi studies [60,62].

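### The stability comparison between the final two rounds names an unpaired test (Wilcoxon rank-sum) for paired ratings, so moderate real shifts will often go undetected

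*Protocol article*

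**What the plan says.** Section 2.5 makes percentage agreement the primary measure and adds one inferential analysis: "Wilcoxon rank-sum tests will be used for the final round to evaluate stability and consistency of responses between the final two rounds". It gives no significance level and no rule for calling an item stable.

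Other sections fix the structure of the data:

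- **Same people.** Under Subject Enrollment (2.3), "each panelist will be asked to commit to participation in each round of the Delphi". Section 2.2 sets the panel size: "We aim to recruit and retain 30 experts from multiple countries".
- **Same answers, revised.** Section 2.4.3 says "In round three, participants can modify their answers from round two based on results and feedback from that round", and that participants are shown "where they answered compared to the group". Section 2.4.2 says the same of round two.
- **Scale.** Section 2.4.1: "Experts will rate their level of agreement for the included items using a 5-point Likert-scale".
- **Items at issue.** Section 2.4.2: "items achieving consensus will not be included in the round three questionnaire". The comparison of rounds two and three therefore covers items that had not yet reached consensus.
- **Linkage.** Section 2.1: "All personal identifiers will be removed from the data sets and replaced with placeholder values".

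**The concern.** The named test treats the two rounds as answers from two unrelated groups. In the design described, the second rating is an edited version of the first, made by the same expert with the first in view. Such ratings should be positively correlated, and a test that ignores the correlation overstates the uncertainty of the change.

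The direction of the error matters here. The purpose is to show that answers have settled, so the natural reading of a non-significant result is that the item is stable. A test that rejects too rarely favours that reading. The items compared are also those still open after round two, where movement is most likely. At stake is the credibility of any statement that panel opinion had stopped moving. This is the only formal between-round test in Section 2.5.

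**Working it through.** The article gives no power or error rate for this test, so there is no figure of its own to reproduce.

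**Inputs from the article:** 30 experts (2.2), a 5-point scale (2.4.1), the same panel in both rounds (2.3, 2.4.3), a 75% consensus line (2.4.1), the rank-sum test (2.5).

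**Assumptions:** two-sided 5% level; non-significance read as stable; within-expert correlation ρ of 0.5 to 0.85 on an underlying normal scale; no loss of experts, with 24 experts (20% loss) as a check.

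**Step 1. Why pairing matters.** Treated as independent, the variance of a mean change is 2σ²/n. For paired data it is 2σ²(1 − ρ)/n. With no true change, a statistic scaled by the first has standard deviation √(1 − ρ) instead of 1. The approximate chance of a false rejection is P(|Z| > 1.96/√(1 − ρ)):

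- ρ = 0.5: 1.96/0.707 = 2.77, about 0.6%
- ρ = 0.7: 1.96/0.548 = 3.58, about 0.03%

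On 5-point ratings the simulated rates are somewhat higher but show the same pattern (Step 3).

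**Step 2. A worked item.** Round two: 16 agree, 14 unsure. Round three: 7 move from unsure to agree and nobody moves back, giving 23 agree and 7 unsure. Agreement goes from 16/30 = 53% to 23/30 = 77%.

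- Rank-sum, tie-corrected. Pooled proportion 39/60 = 0.65. Difference 7/30 = 0.2333. Standard error √(0.65 × 0.35 × 2/30) = 0.1232. z = 0.2333/0.1232 × √(59/60) = 1.88, so p = 0.06.
- Exact paired test. All 7 non-zero differences have the same sign and size, so p = 2 × (1/2)⁷ = 2/128 = 0.016. The normal approximation to the signed-rank test gives 0.008; the exact value is the one to use.

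**Step 3. Simulation** (30 experts, 4,000 runs per setting for the 60% rows; signed-rank by normal approximation in those rows; where runs differed, the range is shown):

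| Change | Test | ρ = 0.5 | ρ = 0.7 | ρ = 0.85 |
|---|---|---|---|---|
| None (type I error) | rank-sum | 0.9–1.4% | 0.1–0.5% | 0–0.03% |
| None (type I error) | signed-rank | 4.5–5.3% | 4.7% | 4.7–5.5% |
| 0.5 SD | rank-sum | 40% | 38–39% | 37% |
| 0.5 SD | signed-rank | 63–66% | 81–83% | 94–97% |
| 60% to 75% agreement | rank-sum | 25% | 24% | 20% |
| 60% to 75% agreement | signed-rank | 50% | 67% | 86% |
| 60% to 85% agreement | rank-sum | 86% | 89% | 93% |

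A further run put rank-sum power at 36–39% for the 0.5 SD shift. With 24 experts, power for the 60% to 75% shift is 21/15/13% for rank-sum and 41/54/75% for signed-rank. At ρ = 0 the two tests perform alike, at about 30% power for that shift with 30 experts.

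**Step 4. Limits of the replacement.**

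- With the exact test, 5 one-way moves give 2 × (1/2)⁵ = 0.0625 and 6 give 2 × (1/2)⁶ = 0.031. Fewer than 6 one-way movers can never be significant at 5%. Power of the exact version is therefore somewhat below the signed-rank rows above, though still well above rank-sum.
- Six moves up and six down, each by one category, give p = 1.0 with both tests, although 12 of 30 experts (40%) changed their answer.

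**The case against.** The strongest reply is that little depends on this test. Consensus is defined by percentage agreement, items are dropped or amended on percentages, unsure ratings or committee review, and Section 2.4.3 ties a fourth round to consensus not being reached. That is correct. In the worked item above, the item passes the 75% rule whichever Wilcoxon test is run, and its percentages would be reported anyway. A reader might infer that the wrong test endangers the consensus findings themselves; the article does not support that.

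A reader might also infer that every real shift will be reported as stability. That is too strong. Rank-sum still detects a move from 60% to 85% agreement in 86–93% of cases over this range of correlation, and more than a third of 0.5 SD shifts. Nor does the article say that a non-significant result means stable; that reading is natural but assumed here.

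Finally, a reader might fault Section 2.5 for not excluding items reworded between rounds. Which items enter the comparison is detail that a condensed article commonly leaves to a fuller plan, and amended items are in any case to be tabulated with explanations. This is not counted against the plan.

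Anonymity does not rescue the unpaired test. In Section 2.5 the word applies to the open-ended answers, and feeding back each expert's own earlier rating already requires a link between rounds.

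**Conclusion.** The point holds as an error in a supporting analysis and should be fixed. The named test does not match the design that the article itself describes, and nothing in the article justifies treating the rounds as independent. That conclusion does not depend on any simulation.

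Its size does depend on assumptions: 30 experts, a two-sided 5% level and correlation of 0.5 to 0.85. Under these the test's real type I error is about 1% or less, and its power for a 0.5 SD shift is about 36–40% against 63–97% for the paired test. A shift from 60% to 75% agreement, enough to reach the consensus line, would be missed 75–80% of the time. If non-significance is taken as stability, moderate shifts will often be mislabelled. Near-zero correlation would remove the loss, but is implausible when experts edit answers they can see.

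**What to change.** In Section 2.5, replace the rank-sum test with the exact Wilcoxon signed-rank test, applied to experts who rated the same item in both of the final two rounds and linked by their placeholder ID. Because offsetting moves cancel in that test and a handful of movers cannot reach significance, report beside it, for each item, the percentage of experts who changed category.

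The cost is a sentence or two in Section 2.5. No new data are needed: the link between rounds must already exist to show experts their earlier answers, and the change touches only the analysis after the final round. The placeholder IDs must be kept in the exported data.

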## 3. Results

We plan to present our results through high-impact publication for the benefit of healthcare professionals, researchers, and patients. Outcomes will be displayed quantitatively (i.e., percentage agreement calculations, and possibly IQR and Median) and qualitatively. At the time of submission of this Delphi study protocol, the first round of this study is planned to begin on or before 1 March 2025.

## 4. Discussion

Dry needling has steadily evolved in clinical practice since its appearance in the literature as far back as the 1940s. Research interest in DN has grown substantially over the last 30 years, with studies investigating the use of DN for headache emerging in the early to mid-1980s [78,91]. At present, a recent meta-analysis study now supports DN as an effective intervention for reducing headache frequency and intensity across a range of headache types, with follow-ups of at least up to 3 months [92].

This study protocol describes the research design for a three, potentially four, round Delphi study to reach expert consensus for recommendations on the use of DN in headache management. The Delphi technique is a firmly established methodology for pursuing consensus on topics related to healthcare, and formulating recommendations based on expert opinion [60,69]. Having consensus-driven recommendations on DN for headaches would assist researchers in designing the methods and protocols for future clinical trials incorporating DN for headaches, and for this reason, a Delphi study will be performed. In addition, clinicians would benefit from having expert recommendations to reference prior to and during the delivery of DN treatments for patients with headaches, as no guidelines currently exist. After reviewing the literature on DN for headache, our observations are much like recent reviews on DN. That is, inconsistencies in DN procedures (i.e., dosage parameters and DN techniques) and practice patterns are prevalent across studies [57,59], especially those studies investigating DN for headache [55].

We also identified wide variations in treatment rationales across studies, with some studies referring to the peripheral mechanisms of DN and others leaning on more spinal or central mechanisms of action. In addition, the clinical indications for DN in headache management also fluctuate across studies. Most of the studies we reviewed administered DN to TrPs for treatment of headache, regardless of headache type. For example, Gildir et al. selected only active TrPs (TrPs that caused the clinical pain compliant when stimulated, i.e., at least part of the headache was reproduced with TrP stimulation) to be needled in patents with TTH [81,93]. Rezaeian et al. performed DN to active TrPs in the sternocleidomastoid muscle (SCM) in patients with migraine [76]. In contrast, Kamali et al. administered DN to TrPs in the suboccipital, temporalis, upper trapezius, or SCM muscles in patients with TTH, without specifying if TrPs elicited headache symptoms upon examination, or if they were latent [82]. A recent study, published after our review of the literature, analyzed the effects of DN on reducing the number of active TrPs in the cranial or facial muscles in patients with TTH, and reported a significant reduction in the total number of active TrPs, along with reductions in headache intensity [94]. None of the studies we reviewed specifically addressed latent TrPs (TrPs that are clinically dormant, are only painful when stimulated, and have similar characteristics as active TrPs) with DN in patients with headaches. Like active TrPs, latent TrPs in the muscles of the head and neck may be a source of local motor dysfunction and peripheral nociception that contribute to muscle pain as well as trigeminocervical and central sensitization [95,96]. It is conceivable that DN may be indicated not only for treatment of active TrPs, but also of latent TrPs in patients with headaches, especially since a recent study found that the pain-relieving mechanisms of DN are intrinsically related to reducing nociceptive input from TrPs, helping to attenuate peripheral sensitization [97]. However, regarding headache management, a multimodal approach that includes DN is recommended considering that nociplastic and neuropathic phenotypes of TrPs may be present, which are related to comorbid factors [25]. Nevertheless, according to a recent systematic review, it remains uncertain whether the TrP should be targeted for DN to be effective in the treatment of headaches [54]. Gaining expert consensus regarding dosage parameters, needling techniques, treatment rationales and clinical indications for the use of DN in headache would be valuable to research and treatment practices. In addition, the insights gained from this Delphi study may also be applicable to the management of various sub-types of headaches.

This Delphi study protocol does have some limitations. First, the questionnaire in its present form does not include items related to psychosocial factors like depression or anxiety, or lifestyle factors, which are relevant in the management of migraine, TTH and CGH. It is possible, however, that certain open-ended questions may lead to the inclusion of such items in other iterations of the questionnaire. Second, survey and questionnaire instruments used in Delphi studies may be subject to certain biases and misinterpretations, which may impact the credibility of the research being performed [98,99]. Third, because most of the research on DN for headache is focused on migraine, TTH and CGH, according to our review of the literature, not all headache types will be investigated in this study. Lastly, while we will include a diverse sample of experts from across the globe, there will be no specific limit to the number of potential experts from one region or country.

